# InterMob: a 24-month randomised controlled trial comparing the effectiveness of an intervention including behavioural change techniques and free transport versus an intervention including air pollution awareness-raising on car use reduction among regular car users living in Grenoble, France

**DOI:** 10.1186/s12889-022-14099-4

**Published:** 2022-09-16

**Keywords:** Daily mobility, Spatial organisation, Psychology, Car use, Active mobility, Sustainable mobility, Behaviour change, Health, Air pollution, RCT

## Abstract

**Background:**

Frequent car use contributes to health and environmental issues such as air pollution, climate change and obesity. Active and sustainable mobility (bike, walk, public transport, car sharing) may address these issues. Different strategies have been implemented in past research, involving *hard* levers, aimed at modifying the economical or geographical context (e.g., free public transport), and *soft* levers, aimed at modifying psychological processes (e.g., personalised transport advice). However, few studies have combined both hard and soft levers. In addition, few have used robust methodologies (e.g., randomised controlled trials), followed behavioural changes in the long-term, and been anchored in behaviour change theories. InterMob aims to address these limits by implementing a 24-month randomised controlled trial including *hard* and *soft* levers. The objectives of InterMob are to a) evaluate the effectiveness of an experimental arm versus an active controlled arm, and b) identify the processes of mobility change.

**Methods:**

Regular car users living in Grenoble (*N* = 300) will be recruited and randomised to one of the two arms. The experimental arm consists in a six-month intervention combining *hard* levers (free access to transport/bikes), and *soft* levers (e.g., personalised transport advice). The control arm consists in a six-month intervention aimed at raising awareness on air pollution and its health effects. Both arms will include eight evaluation weeks (spread out over 24 months) based on a GPS, an accelerometer, and a pollution sensor. Moreover, participants will complete mobility logbooks and surveys measuring psychological constructs, socio-economical, and socio-spatial characteristics.

**Discussion:**

InterMob will assess the effectiveness of two interventions aimed at reducing car use within regular car users in the short-, mid- and long-term. Moreover, InterMob will allow to better understand the psychological processes of behaviour change, and the socio-economical and geographical conditions under which the intervention is efficient in reducing car use. Finally, the benefits of mobility change in terms of physical activity, quality of life, and exposure to pollution will be quantified.

**Trial registration:**

ClinicalTrials.gov: NCT05096000 on 27/10/2021 (retrospectively registered).

**Supplementary Information:**

The online version contains supplementary material available at 10.1186/s12889-022-14099-4.

## Background

Daily car use contributes to major health and environmental issues. Motorised transport represents an important source of air pollution, noise and greenhouse gases [1–3]. Moreover, regular car users present lower levels of physical activity [4], spend more time in sedentary behaviours [5], and have a higher risk of being obese or overweight [6, 7]. In turn, air pollution, climate change and physical inactivity represent important dangers to human health and life expectancy [8–11]. Nevertheless, despite all the negative consequences of daily car use, the car remains the main mode of transport in most countries (e.g., in France, 63% of daily trips are made by car, [12]).

Active and sustainable mobility such as cycling, walking, public transport and carpooling have in contrast positive effects on health and well-being. These modes of transport are associated with higher levels of physical activity [13–16], greater well-being [17], better work performances [18], and a higher life expectancy [19]. In addition, these transport modes might represent an effective lever to tackle air pollution and climate change [20, 21]. Nevertheless, active and sustainable mobility are less frequently used than the car for daily mobility (i.e., in France, 37% of daily trips are made by using an active and sustainable mobility, [12]).

### Strategies for car use reduction, active and sustainable mobility promotion

During the last years, many interventions have been developed to reduce car use and promote active and sustainable mobility. They can be distinguished based on whether they involve *hard* or *soft* levers [22].

*Hard* levers are strategies that target a change in the geographical and economic context of individuals to encourage them to reduce car use and/or increase active mobility. Hard-lever interventions include for example the implementation of low-emission zones (i.e., restricting the entry of polluting motorised transport into an established area), free public transport, city tolls or new cycling and walking infrastructures [23–26]. Results indicate that in general, *hard* levers seem to increase the use of active and sustainable mobility and reduce car use (e.g., implementing a payment for entering to the city centre reduces between 12 and 33% of city-centre cars in European cities, 24, infrastructural interventions in high-income countries increased in median relative, 22% of cycling behaviour compared to the baseline, [26]).

*Soft* levers are strategies that target a change in psychological factors associated with mobility, such as individual’s intention to use active modes of transport, self-efficacy and attitudes towards active mobility, mobility habits, etc. In the behaviour change literature, these levers refer to behaviour change techniques [27]. In the field of mobility, some examples of behaviour change interventions are those proposing personalised transport advice, prompting mobility change goal setting and action planning, furnishing maps, transport schedules and other written materials (for reviews, see [28–30]). The results concerning *soft* levers are more heterogeneous. While a meta-analysis and some systematic reviews show a lack of rigorous studies to allow a conclusion about the effects of these interventions (e.g., [28, 30, 31]).

While past interventions have shown promising results, most of them share the same limitations. First, few studies rely on “robust” methodologies such as randomised controlled trials comparing the effects of an experimental intervention vs. a control intervention (e.g., only 14 studies among 77 studies were identified being “robust”, [31]). Second, few studies were anchored in behaviour change theories, and few describe the behaviour change techniques that were used to elaborate the intervention (e.g., [32–34]). Third, most of the studies use only self-reported measures and no in situ sensors to measure behaviour (except from some exceptions like [35, 36]). Fourth, few studies have mid- and long-term follow-ups (3 months after the intervention or more, e.g., [32, 34, 37–39]). Fifth, most studies focused on only one type of lever, either *hard* or *soft* (e.g., only five interventions among 30 studies were identified as having combined soft and hard levers, [30]). InterMob study aims to address all of these limits.

### InterMob study

InterMob is a study that is part of the interdisciplinary Mobil’Air project that seeks to reduce air pollution in Grenoble, France [40]. More precisely, InterMob study combines concepts and methods from geography, psychology, economics, and epidemiology, with the aim to reduce car use and promote active and sustainable mobility in the Grenoble metropolitan area. InterMob seeks to address the aforementioned limitations by being anchored in behaviour change theories (see Fig. 1). It also relies on a rigorous methodology (a randomised controlled study comparing an experimental and a control group). In addition, it proposes a longitudinal follow-up (8 weeks of measurement spread over 24 months), the experimental intervention contains *hard* and *soft* levers (e.g., free transport and behaviour change techniques), and it combines in situ objective measures and self-reported measurements, in order to collect data on mobility behaviours (e.g., through GPS sensors) as well as on their correlates (e.g., through questionnaires assessing intentions, habits, sociodemographic characteristics, etc.). Moreover, the content of the experimental group is elaborated by mobilising evidence- and theory-based approaches. Indeed, interventions that rely on a theoretical approach appear to be associated with larger effect sizes [41] and more consistent effects [42]. The active control arm includes sensibilisation to air pollution risks (*soft* lever). It targets attitudes, which have been identified as a factor of behavioural intention (e.g., theory of planned behaviour). Such behaviour change technique is expected to be less efficient in changing mobility behaviours than the techniques included in the experimental arm, the latter targeting more directly the intention-behaviour gap.

**Fig. 1 Fig1:**

Followed steps for the elaboration, implementation and evaluation of InterMob. Source: Figure created by authors

In conclusion, InterMob is a 24-months randomised controlled trial, parallel group, two-arm, superiority trial with 1:1 allocation ratio.

The objectives of the study are to:

Evaluate the effectiveness of the InterMob intervention in reducing car use in the short- and in the long-term (one, three, seven, twelve, and twenty-four months after the beginning of the intervention).Identify the mechanisms underlying mobility behaviours and behaviour change (e.g., psychological constructs such as intentions, self-efficacy, habits).Identify the moderators of mobility change (i.e., the conditions and contexts under which the intervention is effective such as family context, degree of cyclability, trip chaining, work situation, activities organisation in space and time).

### Procedure for elaborating, implementing, and evaluating a theory- and evidence-base behavioural intervention

To ensure the theory- and evidence-based character of the study, we followed a framework summarising the methodologies and recommendations already used in health psychology [43–46] (see Fig. 1).

First, we reviewed the literature on the associations between air pollution, physical inactivity, and mobility behaviours. Then, we undertook a literature review in psychology and geography (e.g., [47–50]) on the factors underlying daily mobility behaviour. Third, we carried out an interdisciplinary literature review to identify the strategies that have been successful in reducing car use and increasing active and sustainable mobility [25, 28, 30, 51]. Fourth, we conceived a first version of the InterMob intervention, and conducted a pilot study to test its feasibility. Finally, we established the definitive version of InterMob that is detailed in this article. The present article follows the SPIRIT 2013 Guidance for protocols of critical trials [52, 53].

## Methods

### Ethics and data protection

The Fig. 2 shows the details of the ethics and data protection process. First, InterMob study received the ethic’s approval from Grenoble Alpes Research Ethics Committee (CERGA) in January 2019 (File CER Grenoble Alpes-Avis-2019-01-29-2). Moreover, as part of the application to the Ethics Committee, we carried out a Privacy Impact Assessment (PIA) to assess and avoid any potentially negative impacts of InterMob study on participants’ data privacy. This procedure involved setting a discussion group with the data protection officer of the University, the people in charge of the data infrastructure at the university, and relevant representatives of the target population (members of a car-sharing platform, a local energy and climate agency, and a member of a pedagogical program about air pollution). During the discussion group, we talked about the potential implications of the data-collection tools (e.g., GPS sensors, detailed surveys that include data on psychological constructs as well as the geographic and socio-demographic context), and we detailed the proposed procedures and elements to ensure the respect of the General Data Protection Regulation (RGPD).

**Fig. 2 Fig2:**
[figure not shown]
Procedure of the InterMob study since the ethics and data protection procedures to the study enrolment and beginning of the study. Source: Figure created by authors

### Participants

#### Study setting

To detect the effects of InterMob study on car use reduction, recruitment will be restricted to individuals living and working in the Grenoble metropolitan area (see Fig. 3), an urban area of south-eastern France (in the Alps) with a population size of approximately 600,000 people. The topography of this area is characterised by being flat in the valleys (especially the Grenoble city) and surrounded by mountains (suburban areas). Car is the main transport mode for daily trips (53% of daily trips in the Grenoble metropolitan area are made by car, [54]).

**Fig. 3 Fig3:**
[figure not shown]
Map of InteMob study area. Map generated by authors from IGN BD TOPO and BD ALTI®

#### Eligibility criteria

To take part in the InterMob study, participants will need to meet the following criteria:Being 18 years and older at the time of the eligibility interview;Living, working, studying, in the Grenoble metropolitan area;Having a car or motorbike as the main transport mode during the week (excluding the weekends);Travelling at least 3 days a week (excluding the weekends) by car or motorbike;Motivated to reducing car use for daily trips, or having already started this reduction (i.e., being in the contemplation, preparation or action stages of change according to [55, 56]);Expecting to stay in the Grenoble metropolitan area for the duration of the study (24 months).

All the eligibility criteria have been established by considering theoretical and practical aspects. For instance, theories in psychology suggest that participants who intend to change their behaviours do not need the same behavioural techniques than those not having such intention (e.g., [57, 58]). More precisely, one of the main goals of behaviour change approaches is to help people to overcome the intention-behaviour gap [59].

### Participant timeline

#### Recruitment, allocation, and blinding

The participants will be recruited through different sources: mailing lists from former studies conducted by the research team (QAMECS-SHS and EMC^2^ 2019–2020, local travel surveys, surveys from other laboratories and projects), publicity in local events related to transport or environment, publicity in community newspapers, interventions with the mobility referents of companies in the Grenoble region and, social networks (e.g., Facebook, LinkedIn and Instagram). The people that will be interested to participate in the InterMob study will fill up an online form in order to be contacted by a member of the implementation team (the information in this form includes the first name, a telephone number, an email address, municipality of residence, sex, age, educational attainment and the availability for receiving a phone call). The implementation team will call interested people to explain the study procedure and to administer the eligibility questionnaire. A few days later, the implementation team will call again the eligible people to ask if they accept to participate in the study. If a participant accepts, she/he will be randomly allocated to the experimental or active control arm. For this allocation, a randomisation list for the whole study was created by blocks of six before the beginning of the enrolment (i.e., it exists three possibilities to be in the experimental arm and three possibilities to be in the active control arm) by a member of the scientific team. The list was implemented in the management tool software developed by the team with WebDev for the study. The management tool automatically assigns each eligible participant to a group (the n-th participant is assigned to the group corresponding to the n-th position of the list).

Concerning blinding, the implementation team (programme implementers) will not be aware of group allocation at baseline (S0), but blinding will be impossible afterward, as the programme implementers deliver different contents to each arm through face-to-face interviews with participants. The researchers will not be aware of group allocation at any time, and the researchers responsible for analysing the data will be blinded to the treatment allocation. Double blinding will not be possible given that allocation concealment is impossible for participants in such an intervention.

#### Timeline of the study

Participants enrolled in the study will have a first two hours with a programme implementer (“Session 0” or S0, see Fig. 4). At the beginning of this meeting, the participant reads and signs an informed consent form (cf. Supplementary materials). She/he fills up a first questionnaire assessing her/his quality of life, biometrics, mobility behaviours, the weekly duration of moderate-to-vigorous physical activity, socio-demographic information and psychological constructs 1, 2 and 3, as well as a mobility logbook assessing her/his last week mobility (for more details about the tools and surveys, see Table 1). Then, the implementation team explains how to correctly carry the Sensedoc™ and MicroPem™ sensors (see Fig. 5), and the participant is instructed to start carrying them from the next 7 days. At the end of the session, the sensors are collected by the programme implementer. Moreover, during this session, the participants receive a daily survey on their telephones measuring psychological constructs 4. Two weeks after S0, the participants have the first intervention appointment (S0+) that will be described in the intervention subsection.

**Fig. 4 Fig4:**
[figure not shown]
Calendar of the intervention and the measurements. S = Session (seven-day measurement), M = Month, ap = appointment being part of the intervention. The icon of the green notebook represents seven days of carrying a Sensedoc and a MicroPem (the air pollution sensor is only carried during the sessions 0, 3 and 6), the icon of the GPS represents seven days of filling up a mobility logbook, answering a long survey (one time) and a short daily survey. Source: Figure created by authors

**Table 1 Tab1:** Summary of the outcomes, tools and time measurements

Outcome	Tool	Time measurement									
		R	S0	S0+	S1	S2	S3	S4	S5	S6	S7

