**Fig. 5 Fig5:**
[figure not shown]
Data collection sensors. In the left side, Sensedoc™ sensor (Accelerometer and GPS) which should be worn in a belt around the waist. In the middle, MicroPem™ (pollution sensor) which should be worn in a bag or purse with the pipe as close to the airway as possible. In the right side, the MicroPem™ and the Sensedoc™. Source: Figure created by authors

Approximately 1 month after the beginning of the study, participants have the second meeting of the intervention (1 hour) and start a new session of measurement (S1). During this session, they carry a Sensedoc™ and answer the same surveys as in S0. Approximately 3.5 months after the start of the study, the participants have the third session (S2) containing the same elements as in S0 except for the pollution sensor. Then, about 7 months after the start of the study, the intervention is finished and immediately after the end of the intervention, the participants have the fourth session (S3) during which they carry the Sensedoc™ and the MicroPem™ and answer the same surveys as in S0. Around 9 months after the start of the study, participants start the fifth session (S4), they do not carry any sensors but fill up a mobility logbook and answer the same as in S0. Twelve months after the start of the study, participants start the sixth session (S5) with the same protocol as S4. Eighteen months after starting the study, participants start the seventh session (S6) following the same protocol as S0. Finally, 24 months after starting the study, participants start the eighth session (S7) and follow the same protocol as S4 and S5 (see Fig. 4).

All the sessions are scheduled with our management tool by considering the availability of the programme implementers. This internal tool is central to implement and chart all steps of the intervention.

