#### Secondary outcomes and data collection methods

Secondary outcomes will include the following variables associated with mobility behaviours: kilometres travelled by active and sustainable mobility, and the modal share of active mobility, physical activity measured by the Sensedoc™ 2.0 sensor and the IPAQ (i.e., International Physical Activity Questionnaire, [60]), exposure to air pollution (i.e., concentration of fine particles PM_2.5_ and oxidative potential) measured by an air pollution sensor (MicroPem™), activity programme measured by the mobility logbook and, quality of life measured by a survey [61] (see Fig. 5).

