#### Statistical methods

##### Analysing the effects of the intervention on primary and secondary outcomes by using multilevel modelling

The analysis of the effectiveness of the intervention on the primary outcome (reduction of car use, see "Primary ouctome and data collection methods") and secondary outcomes (mobility-related variables described in the section "Secondary outcomes and data collection methods") will be examined at the very short term (3 months after the start of the intervention: S2), the short term (7 months after the start of the intervention: S3), the medium term (1 year after the start of the intervention: S5) and the long term (18 months after the start of the intervention: S6). More precisely, we will test the differences in car use reduction between the experimental arm and the active control arm, by using multilevel modelling, which is appropriate when data are nested, as it is the case here with several measurement times per participant (e.g., [78]). Moreover, multilevel modelling offers the possibility to analyse incomplete data sets, which is particularly relevant given the duration of the study, which makes likely the occurrence of missing data [79]. For this purpose, we will follow the steps recommended by [80]:Prepare the data by differentiating between- and within-individual constructs.Centre the within-individual variables by participant (i.e., “group centring”).Create a first “constraint” model (a model containing all the random and fixed variables of the final model) and a “null” model including only the “intercept” equal to 1 and only one random variable associated with the identity of the participant (i.e., 1 | Id) to check the intraclass correlation coefficients (ICC).Build the main model.Evaluate the normal distribution of residuals, Cooks distance and influential cases.

The main model will include the following fixed effects: arm, time, and arm x time interaction, with random intercepts for participants and random linear slopes for repeated measures at the participant level.

Moreover, the statistical analysis will follow intention-to-treat principles. This means that once a participant has been randomly assigned to an arm (i.e., experimental or control), his/her data will be included in the analysis [81]. More precisely, even if a participant has not adhered to the intervention or has not finished the study, his/her data will be included to all the analysis.

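### Both pollution-exposure follow-ups fall 5 to 6 months out of season with baseline and the stated model has no calendar term, so staggered enrolment would cost the arm comparison precision

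*Protocol article*

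**What the plan says.** Exposure is a secondary outcome, defined under Secondary outcomes and data collection methods as "exposure to air pollution (i.e., concentration of fine particles PM_2.5_ and oxidative potential", the latter two measured with the MicroPem. The Fig. 4 caption limits it to three sessions: "the air pollution sensor is only carried during the sessions 0, 3 and 6". Table 1 agrees.

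Timeline of the study dates these sessions. For S3: "about 7 months after the start of the study, the intervention is finished", with the session immediately afterwards. For S6: "Eighteen months after starting the study, participants start the seventh session (S6) following the same protocol as S0". The sessions that share the baseline season do not measure exposure. For month 12: "Twelve months after the start of the study, participants start the sixth session (S5) with the same protocol as S4", and S4 has no sensors. S7 at month 24 follows the same pattern.

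Statistical methods gives one model for primary and secondary outcomes: "The main model will include the following fixed effects: arm, time, and arm x time interaction", with random intercepts and random linear slopes per participant. No season, date or ambient-level term is named. The effect tested is between arms: "we will test the differences in car use reduction between the experimental arm and the active control arm". The Abstract also promises that "the benefits of mobility change in terms of physical activity, quality of life, and exposure to pollution will be quantified".

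**The concern.** A seven-day personal PM2.5 reading includes whatever background prevails that week. The protocol itself treats air quality as changing over weeks, since the control arm discusses recent air quality and logs pollution peaks. With follow-ups at months 7 and 18, a participant who starts in winter has both exposure follow-ups in summer or close to it, and the reverse.

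In the model, time runs from enrolment. If participants enter at different times of year, the yearly cycle has a different phase for each of them. Neither a common time effect nor a participant-level linear slope can represent that, so the variation goes into the error of the arm contrast. The precision of the exposure comparison is at stake and, to a lesser degree, that of the mobility and activity outcomes at S2, S3 and S6. Separately, a mean change from S0 within one arm would mix season with any effect of changed travel.

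**Working it through.** **Inputs from the protocol.** Exposure sessions at months 0, about 7 and 18. Sessions without sensors at months 12 and 24. S2 at about 3.5 months. Fixed effects arm, time and arm x time. Randomisation 1:1 in blocks of six in order of enrolment. Target of 150 per arm.

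**Inputs the protocol does not give (assumptions).** Yearly amplitude A of the outcome, non-seasonal within-person SD s per session, and length of the enrolment window. Results are therefore shown over ranges.

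The protocol has no figure for exposure or season to reproduce. Its sample size calculation concerns car trips at the end of the intervention and is not touched by this point; 150 per arm is used below only as the arm size.

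**Step 1: offset from the baseline season.** Month 7 is 12 - 7 = 5 months away. Month 18 is 18 - 12 = 6 months away. Months 12 and 24 are 0 away.

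**Step 2: seasonal swing in change from S0.** With season written as A cos(2πd/12) for calendar date d in months, the seasonal part of a change over m months is a sinusoid in the start date with amplitude 2A|sin(πm/12)|. This gives 1.59A at m = 3.5, 1.93A at 7, 2.00A at 18, and 0 at 12 and 24. The exposure schedule is at or near the maximum.

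**Step 3: effect on the arm contrast with year-round enrolment.** The seasonal variance of a change is half the squared amplitude, 2A² sin²(πm/12): 1.87A² at month 7 and 2.00A² at month 18. The non-seasonal variance of a change is 2s². The variance of the arm difference in change is therefore inflated by 1 + (A/s)² sin²(πm/12), with sin² = 0.933 at month 7 and 1 at month 18. A calendar term removes the share 1 - 1/inflation.

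| A/s | Inflation, month 7 | Share removed | Inflation, month 18 | Share removed |
|---|---|---|---|---|
| 0.3 | 1.08 | 8% | 1.09 | 8% |
| 0.5 | 1.23 | 19% | 1.25 | 20% |
| 1.0 | 1.93 | 48% | 2.00 | 50% |
| 2.0 | 4.73 | 79% | 5.00 | 80% |

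On the standard-error scale at month 18, the first three rows are reductions of 1 - 1/√1.09 = 4%, 1 - 1/√1.25 = 11% and 1 - 1/√2 = 29%. A simulation of the month 18 figures gave 8%, 22% and 47% of the variance for A/s = 0.3, 0.5 and 1.0.

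**Step 4: dependence on the enrolment window.** Simulated standard error of the arm difference in change, 150 per arm, in units of s (month 7 / month 18), without a calendar term:

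| Window | A/s = 0.5 | A/s = 1.0 | A/s = 2.0 |
|---|---|---|---|
| All start together | 0.163 / 0.166 | 0.163 / 0.166 | 0.163 / 0.166 |
| 3 months | 0.166 / 0.169 | 0.179 / 0.179 | 0.226 / 0.216 |
| 6 months | 0.176 / 0.183 | 0.217 / 0.229 | 0.337 / 0.360 |
| 12 months | 0.179 / 0.184 | 0.225 / 0.231 | 0.353 / 0.366 |

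Without any season the formula gives √(4/150) = 0.163. With sine and cosine of the date in the model, the standard error is about 0.16 for windows of 3, 6 and 12 months and every amplitude. The simulated arm contrast stayed within 0.01s of its true value of zero in every case, so there is no bias.

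**The case against.** The strongest case against the point is that nothing planned is biased. Allocation in blocks of six by enrolment order gives the two arms the same calendar distribution, and the planned test is already the difference between arms. That stands, and it limits the point to precision.

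It is also fair that the loss is conditional. If everyone starts in the same weeks, the seasonal shift is common to all and drops out of the arm difference. The protocol states no window. It does say that recruitment continues until resources are exhausted, that S0 is a two-hour meeting, and that sessions depend on the implementers' availability. Staggered entry is therefore likely, but it is an inference.

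A third objection is that covariates belong in a statistical analysis plan and that the article does not say its list of effects is exhaustive. That is true, and an unseen plan may already adjust for season. But the sensor calendar and the fixed effects are both stated, and the stated pairing can be improved cheaply.

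Three stronger readings are tempting and not supported. A reader might infer that season overwhelms the within-person change, or that the observed changes are mostly seasonal. The protocol gives no amplitude, SD or expected exposure effect, and at A/s = 0.3 the gain is only 4% of the standard error. A reader might also infer that comparing S3, S5 and S6 to judge whether the effect lasts is distorted. An additive seasonal effect cancels between arms at each session, so it is not. Only an effect of the intervention that itself varied by season could do that; nothing in the protocol establishes one, and additive calendar terms would not correct it. For car use, moreover, month 12 is both measured and analysed, so a same-season contrast exists.

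**Conclusion.** The point holds as a matter of precision and interpretation, not of bias. Both exposure follow-ups are 5 to 6 months out of season with baseline, no season-matched exposure measurement exists, and the stated model has no term that would take season out. Under a single yearly cycle and enrolment spread evenly over a year, a calendar term would recover about 8%, 20% or 50% of the variance of the arm difference in change at month 18 for A/s = 0.3, 0.5 or 1.0. The gain falls as the window narrows and is zero for a simultaneous start. The documents do not say where in this range the trial lies.

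The mobility and activity outcomes at S2, S3 and S6 are exposed to the same mechanism, with the size again unknown. The target of 300 participants is unaffected. The Abstract's promise to quantify exposure benefit names no method; a change from S0 within one arm would not support it.

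**What to change.** In the main model, add sine and cosine of the date of each measurement week (or calendar month) as fixed covariates for exposure, and likewise for the mobility and activity outcomes. For PM2.5, optionally add the ambient background concentration over the same seven days. Keep the between-arm contrast as the only basis for an exposure benefit, and state that within-arm change from S0 will not be read as an effect of mobility change. Specify this before the outcome data are analysed.

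The measurement schedule need not change. Sessions are already scheduled in the management tool, so the dates are at hand. The cost is two or three extra model terms and, if the ambient level is used, retrieval of station data for the measurement weeks.
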